## Abstract

**Background:**

The early onset of myopia in children has become a critical public health issue that requires urgent attention. Notably, high myopia-related retinal diseases have emerged as the leading cause of irreversible blindness in adults in certain regions of China. Physiological hyperopia, as a protective factor and one of the strongest predictors of myopia development, plays a key role in delaying the progression of early-onset myopia and reducing the risk of high myopia in adulthood. However, the dynamic changes, critical turning points, and factors contributing to the rapid regression of physiological hyperopia during childhood remain unclear.

**Objective:**

This study aims to explore the key influencing factors for children’s physiological hyperopia fading and myopia onset, as well as the protective mechanisms of physiological hyperopia against myopia.

**Methods:**

This was a prospective nested case-control study. Our research team previously established a prospective cohort of 2109 preschool children, aged 3 to 6 years, through cluster sampling in 22 kindergartens in Haidian District, Beijing, and completed a 3-year follow-up. Building on this cohort, this study adopts a prospective nested case-control design. We will continue to follow up this cohort with a 3-year longitudinal study, tracking children aged 6 to 9 years. During the 3-year follow-up period, participants will undergo annual eye examinations and complete questionnaires regarding their living habits and environment. The primary outcome is incident myopia, while secondary outcomes include the prevalence of myopia and the changes in various ocular biological parameters. The study received ethics approval on April 7, 2024, from the Ethics Committee of Beijing Tongren Eye Center, Beijing Tongren Hospital (TREC2024-KY034) and was registered on July 5, 2024.

**Results:**

Participant recruitment began on July 10, 2024, and is expected to be completed by December 31, 2026. As of February 2026, recruitment is ongoing, and the final results are expected by December 2026.

**Conclusions:**

This prospective nested casecontrol study investigates the dynamic changes and regression patterns of physiological hyperopia in school-aged children and evaluates the associations between ocular biometric parameters and the onset of myopia. The findings are expected to support standardized myopia screening, inform clinical interventions, and provide evidence-based guidance for government policies on myopia prevention and control in young children.

## Introduction

Myopia is a major global public health problem and is projected to affect approximately 50% of the world’s population by 2050 [1]. It is the most common ocular condition in many Asian countries, with prevalence rates substantially higher in regions such as China, Singapore, Hong Kong, and Taiwan than in Western countries [2,3]. A 2025 nationwide analysis of more than 5 million Chinese children and adolescents reported a persistently high prevalence of myopia, with a steep age-related increase and projections indicating a continued rise in high myopia, highlighting the long-term public health burden in China [4].

Myopia adversely affects the physical and psychological well-being of children and adolescents and may lead to serious ocular complications, including retinal detachment, macular degeneration, glaucoma, and cataract [5-7]. In some regions of China, high myopia-associated retinopathy has become the leading cause of irreversible blindness in adults [8], resulting in a marked reduction in quality of life. Myopia is an irreversible ocular condition, and treatment options are limited to controlling its progression and preventing complications after onset [9]. Therefore, early prevention and intervention of myopia in children in China are urgent public health priorities.

Physiologically, newborns typically present with hyperopia, with an average refractive error of approximately +2.50 to +3.00 diopters (D). With increasing age, hyperopia gradually decreases and progresses toward emmetropia (−0.50 to +0.50 D) [5]. However, environmental and behavioral changes in modern society—including increased exposure to artificial lighting, widespread use of electronic devices, reduced outdoor activity, and intensified early educational demands—have substantially altered this developmental process [10-13]. In some children, these factors lead to an early onset of emmetropia, which often persists only briefly before progressing to myopia. This premyopic hyperopic state, referred to as physiological hyperopia, may serve as an important predictor of early myopia onset [14]. From an epidemiological perspective, reducing disease incidence is central to effective prevention. In childhood myopia, this strategy translates into preventing myopia among children who are not yet affected. Accordingly, the trajectory of physiological hyperopia during early childhood represents a critical target for myopia prevention. However, the mechanisms underlying physiological hyperopia changes, the timing of critical transition points, and the factors driving rapid physiological hyperopia regression and subsequent myopia development remain poorly understood.

In China, childhood myopia screening and prevention are guided by national public health policies. The Myopia Prevention and Control Guidelines (2024 edition) issued by the National Health Commission recommend regular vision screening in kindergarten and primary school settings and emphasize early identification of children at risk for myopia. These national recommendations are implemented locally through school-based vision screening programs in cities such as Beijing. However, evidence on the longitudinal trajectory of physiological hyperopia and its transition to myopia during the critical preschool to school-age period remains limited.

Therefore, this study conducted a nested case-control investigation among school-aged children in the Haidian District of Beijing to establish a cohort of children with physiological hyperopia. The baseline values of refractive error, visual acuity, axial length (AL), anterior chamber depth (ACD), corneal radius (CR), and other ocular biometric parameters were recorded following cycloplegia. Through longitudinal follow-up, this study aims to identify key factors influencing physiological hyperopia regression and myopia onset, as well as to explore the protective role of physiological hyperopia in myopia development. The findings are expected to provide evidence to inform population-level strategies for early myopia prevention and control.

## Methods

### Objective

This study aims to explore the key influencing factors for children’s physiological hyperopia fading and myopia onset, as well as the protective mechanisms of physiological hyperopia against myopia.

### Study Design

This study is a prospective observational study based on an established cohort, with planned nested case-control analyses embedded within the longitudinal follow-up framework. All participants are followed annually using standardized ophthalmic examinations and questionnaires. Incident myopia cases identified during follow-up are used for the primary inferential analyses through risk-set matched nested case-control sampling, while cohort-level and cross-sectional analyses are conducted to describe longitudinal refractive and biometric changes. The primary inferential analyses are conducted using risk-set matched nested case-control sampling focused on incident myopia. The study period spans from January 1, 2024, to December 31, 2026, and the protocol is registered at ClinicalTrials.gov (NCT06498947).

Our research team previously established a prospective cohort of 2109 preschool children, aged 3 to 6 years, through cluster sampling in 22 kindergartens in Haidian District, Beijing, and completed a 3-year follow-up. Building on this established cohort, this study continues prospective follow-up as children transition into school age (6‐9 years), with annual ophthalmic examinations and questionnaire-based assessments.

Although all participants are followed longitudinally, the primary scientific objective of this study is not to model population-average trajectories alone, but to identify factors associated with the transition from physiological hyperopia to incident myopia during this critical developmental window. For this purpose, a prospective nested case-control design was selected as the main inferential strategy within the cohort framework.

The nested case-control study is an innovative research method that combines elements of traditional case-control and cohort studies, and its validity has been demonstrated in multiple large-scale studies [15-17]. Nested case-control sampling enables efficient and focused comparison between children who develop myopia and those who remain nonmyopic at the same follow-up time point, thereby preserving the temporal sequence between exposure and outcome while minimizing selection bias. In addition, key exposures of interest—such as baseline hyperopic reserve and the rate of physiological hyperopia regression—are age dependent and time varying. Risk-set matching within the cohort facilitates appropriate control for age and follow-up time and supports robust multivariable modeling of detailed exposure profiles.

Case-control sampling is performed only when new cases of myopia are identified during follow-up. Each incident myopia case is matched in a 1:1 ratio with a control selected from cohort members who remain at risk at the same time point. Cross-sectional analyses conducted at each follow-up visit are intended solely for descriptive and exploratory purposes and do not constitute part of the primary inferential analyses.

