### Study Setting and Participants

This study focuses on school-aged children in Haidian District, Beijing, and includes a 3-year prospective follow-up. As the educational and technological hub of northwest Beijing, Haidian District has a well-established education management system, facilitating research coordination. Furthermore, the high level of parental compliance with myopia prevention measures in the region ensures the successful implementation of long-term follow-up.

Infants typically exhibit a hyperopia of +3.0 to +4.0 D, which transitions into a period of rapid development before the age of 3 years, followed by a slower developmental phase. By approximately 12 years, the process of emmetropization is gradually completed. On the basis of this developmental pattern, this study focuses on school-aged children as the target population. For this study, children aged 6 to 9 years who met the eligibility criteria were invited to continue annual follow-up examinations for an additional 3 years. Figure 1 illustrates the overall participant flow, including cohort enrollment, eligibility assessment, annual follow-up visits, and identification of incident myopia cases for nested case-control analyses. Textbox 1 lists the inclusion and exclusion criteria.

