### Statistical Analysis Plan

In this project, the basic statistical design plan was a prospective nested case-control study, as shown in Figure 2. Statistical analyses will be conducted according to prespecified research questions and outcomes. Analyses will include descriptive analyses, primary inferential analyses for incident myopia, and secondary analyses for longitudinal changes in ocular biometric parameters.

Descriptive analyses will summarize participants’ baseline characteristics and annual follow-up measurements, including refractive status and ocular biometric parameters. Continuous variables will be reported as means (SDs) or medians (IQRs), as appropriate, and categorical variables will be summarized as frequencies and proportions. The distribution of continuous variables will be assessed using graphical methods (eg, histograms and Q-Q plots) and the Shapiro-Wilk test.

The primary inferential analysis will evaluate the association between physiological hyperopia and incident myopia. A nested case-control approach will be applied, in which children who develop myopia during follow-up will be identified as cases and matched in a 1:1 ratio with controls selected from cohort members who remain nonmyopic at the same follow-up time point. Conditional logistic regression models will be used to estimate odds ratios and 95% CIs, adjusting for potential confounders, including age, sex, parental myopia, time spent in outdoor activities, and time spent on near-work activities.

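### Risk-set matching is credited with helping to control for age, but the matching rule uses only the follow-up visit, so all age control rests on the model covariate

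*Protocol article*

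**What the plan says.** The protocol article's Study Design section observes that the main exposures, hyperopic reserve at baseline and the speed at which it is lost, vary with age and over time. It then states: "Risk-set matching within the cohort facilitates appropriate control for age and follow-up time". The same sentence adds that matching supports multivariable modelling.

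The sampling rule appears twice:

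- Study Design, 1:1 for each case: "a control selected from cohort members who remain at risk at the same time point".
- Statistical Analysis Plan: "controls selected from cohort members who remain nonmyopic at the same follow-up time point".

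Neither statement has an age band, caliper or birth-date criterion.

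Age enters the primary analysis in Statistical Analysis Plan as a covariate in the conditional logistic model: "adjusting for potential confounders, including age, sex, parental myopia, time spent in outdoor activities, and time spent on near-work activities". The form of the age term is not given.

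On who is in the risk sets, Study Setting and Participants says "children aged 6 to 9 years who met the eligibility criteria were invited to continue annual follow-up examinations for an additional 3 years". Textbox 1 has the same age range as an inclusion criterion. The source was a "prospective cohort of 2109 preschool children, aged 3 to 6 years", already followed for 3 years.

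**The concern.** A visit number measures time since enrolment, not attained age. At the first annual visit, a child who entered at 6 is about 7 and a child who entered at 9 is about 10, and the stated rule lets one serve as the control for the other. The rule delivers the follow-up-time half of the Study Design claim and not the age half.

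Age matters here on the article's own evidence. Study Design calls the exposures age dependent. Sample Size Calculation cites a myopia prevalence of 5.9% at age 6 against about 36% on average in primary school. The Discussion cites a rise in incidence from age 7, which lies inside the enrolled range. If matching does not balance age, the primary odds ratio depends on the age term being specified adequately, and a reader who trusts the Study Design sentence would not know that.

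**Working it through.** **1. Claim against rule.** The article gives no figure for the case-control age gap, so there is none to reproduce; the texts are compared directly.

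| Property credited to matching | Criterion in the rule | Delivered by matching? |
|---|---|---|
| Follow-up time | Same visit | Yes |
| Age | None | No |

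**2. Age gap within pairs.** Visits are annual, so two children seen at the same visit differ in age by what they differed at entry. For two children drawn independently from a uniform age band of width W years:

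- P(gap > 1 year) = ((W − 1)/W)²
- mean absolute gap = W/3

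W = 3 (ages 6 to 9): (2/3)² = 44%, mean 1.0 year. 
W = 4 (if 9-year-olds count up to their tenth birthday): (3/4)² = 56%, mean 1.33 years.

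The article gives no age distribution, so other shapes were simulated, with the odds of myopia constant or rising up to 2-fold per year of age (assumed):

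| Assumed entry ages | Pairs more than 1 year apart |
|---|---|
| Clustered at 7.5 (normal, SD 0.6) | 24–26% |
| Triangular, 6 to 9 | 26–28% |
| Uniform, 6 to 9 | 44–47% |
| Uniform, 6 to under 10 | 56–60% |

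**3. What controls age.** Simulation with 915 children (the minimum cohort in Sample Size Calculation). Assumed: ages uniform 6–9, baseline refraction mean +1.2 D and SD 0.8, falling 0.3 D per year of age; log odds of onset +0.4 per year of age; true log odds ratio −1.5 per D; three annual visits; about 210 pairs; 300 replicates.

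| Matching | Age term | Mean log OR | SD |
|---|---|---|---|
| Visit only | none | −1.62 | 0.226 |
| Visit only | linear | −1.53 | 0.247 |
| Visit and ±0.5 year | none | −1.53 | 0.221 |
| Visit and ±0.5 year | linear | −1.54 | 0.227 |

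With visit-only matching, the estimate moves from −1.62 to −1.53 only when the covariate is added. The remaining 0.03 from the true value is common to both designs. Variance ratio, visit-only to age-matched, both with the age term: (0.247/0.227)² = 1.18.

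**4. Dependence on the form of the age term.** Adding a U-shaped age effect to the step 3 model, with only a linear term fitted, gave −1.49 against the true −1.5, so non-linearity need not do harm.

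A second simulation generated refraction directly. Assumed: 1006 children aged 6.0–9.99, mean +1.5 D at age 6 falling 0.28 D per year of age, SD 0.7, onset at −0.50 D or below, about 300–390 pairs. Median log OR per D of baseline hyperopia:

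| Hyperopia loss | Visit only + linear age | Age-matched ±6 months | Difference | Variance ratio |
|---|---|---|---|---|
| Constant | −4.14 | −4.12 | under 1% | (0.61/0.57)² = 1.15 |
| Rising with age | −4.25 | −4.14 | 3% further from 0 | (0.66/0.51)² = 1.67 |
| Peaked near 8.5 years | −3.93 | −4.34 | 0.41/4.34 = 9% nearer 0 | no gain |

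In the peaked case a quadratic age term with visit-only matching gives −4.19, recovering 0.26 of the 0.41. A separate check over 3- and 4-year age spans gave variance ratios of about 0.8–1.3 and 4–6% attenuation, in the peaked scenario only. A simpler logistic-hazard simulation gave variance ratios of 0.90–1.18 and little bias.

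**5. Enough controls?** With an assumed 500–900 children at risk, a 1-year window holds about 500 × 1/4 = 125 to 900 × 1/3 = 300 potential controls, and about half that at the ends of the age range.

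**The case against.** The strongest reply is that the article does control for age, by a standard method. The key verb is only that matching facilitates control, the same sentence points to modelling, and age is the first covariate listed. All of that is true, and it is why the estimate is sound when the age term is adequate. It does not rescue the sentence: under the stated rule matching facilitates nothing with respect to age.

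A reader might infer that the hyperopia odds ratio is biased, or that any non-linear age effect pulls it towards 1. The documents do not support that. The form of the age term is not stated, and leaving it to an analysis plan is normal. In the simulations the shift was towards 1 in the peaked scenario, slightly away from 1 in the rising one, and negligible otherwise. The 9% figure also takes the age-matched estimate as its reference, not a known true value. Nor is a variance penalty of 1.5 or more established, since the other checks centre near 1.

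The age-gap percentages rest on assumed distributions. The Abstract could be read as children passing from 6 to 9 during follow-up; with entry ages spanning only 1.5 years, about 11% of pairs would differ by more than 1 year. But Study Setting and Participants and Textbox 1 both make 6 to 9 the range at entry.

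Finally, a condensed article may leave calipers to a fuller document, and Figures 1 and 2 could not be seen. This point does not rest on a missing detail: the rule is stated twice, in terms that do not deliver the property claimed.

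**Conclusion.** The mismatch holds. The article credits risk-set matching with helping to control for age, while its rule conditions only on the visit, among children who enter over a span of about 3 years. Matching provides no age control, and the covariate provides all of it.

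The consequence is modest. About 44% of pairs differ by more than 1 year if ages are uniform over 6 to 9, and roughly 24% to 60% under the other shapes tried. With a well-specified age term the primary odds ratio is close to unbiased. With a linear term and a non-monotone age effect it can be off by about 4% to 9% in assumed scenarios. The precision gain from age matching ranges from nil to moderate. Adding age to the matching is a worthwhile, inexpensive improvement, not the repair of an invalid analysis.

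**What to change.** In Study Design and in Statistical Analysis Plan, change the rule so that each case is matched 1:1 with a child who is free of myopia at the same visit and whose age at that visit is within about 6 months of the case's. Forming risk sets on attained age is equivalent. Keep age in the conditional logistic model for the residual difference.

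The cost is one sentence in each place and no new data: the whole cohort is examined annually, and the Results section says analysis starts only after data collection, so controls can still be drawn this way. There are two downsides. The effect of age can no longer be read from the matched pairs, though the cohort-level descriptions still show it. An occasional case, mainly at the ends of the age range, may need a wider window.

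If matching stays on visit alone, remove age from the Study Design claim and say that age is controlled by covariate adjustment.

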### Examinations

Parameters measured included cycloplegic refraction, recording of refractive changes, visual acuity, postdilated refraction, AL, ACD, CR, eye position, fundus, height, and weight.

All the abovementioned metrics were collected at each follow-up visit, and data were collected annually for a specified period.

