### Data Collection and Follow-Up

This study does not involve any intervention. All procedures are observational and consist of standardized ophthalmic examinations and questionnaire-based assessments conducted at baseline and at each annual follow-up visit. The following biological parameters were measured annually in children in the cohort: visual acuity, cycloplegic refraction, AL, ACD, CR, ocular position, fundus, height, weight, and other parameters.

First, visual acuity was assessed using the Early Treatment Diabetic Retinopathy Study visual acuity chart at a distance of 4 m, with the 1.0 line at eye level. Visual acuity was assessed monocularly, with one eye covered without applying pressure while the other eye was tested. Measurements were performed in a right-to-left sequence. The number of correctly identified letters was determined by reading optotypes from top to bottom.

Second, cycloplegic refraction was performed using 1% cyclopentolate hydrochloride. Initially, 1 drop of 0.4% oxybuprocaine hydrochloride (as topical anesthetic) was instilled. Following a 3-minute interval, 1% cyclopentolate hydrochloride eye drops were administered at 5- to 10-minute intervals for 3 consecutive doses. Pupillary diameter and light reflex were assessed 30 minutes after the final instillation. Complete cycloplegia was defined as pupillary dilation ≥6.0 mm and absence of pupillary light reflex (grade 0 on the standardized light reaction scale). Participants meeting these criteria underwent automated refraction using a calibrated autorefractor (Nidek ARK-1), with triplicate measurements obtained under mesopic conditions (3 cd/m²).

Third, ocular biometric parameters, including AL, CR, and ACD, are measured using an optical interferometric AL meter (AL-Scan, Nidek Co, Ltd). The AL to CR ratio is calculated as AL-to-CR=AL/mean CR. The device automatically obtained multiple measurements and reported averaged values.

Fourth, eye position was assessed using masking-demasking and alternating masking methods to screen for strabismus. The direction of ocular movement was assessed to determine whether the participant had strabismus or occult strabismus.

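### The primary analysis of incident myopia keeps one sampled control per case although every child already has the exposure data: valid, but it gives up about 40 to 47% of the information for weak effects and more for strong ones

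*Protocol article*

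**What the plan says.** The protocol article, Study Design, sets the sampling: "Each incident myopia case is matched in a 1:1 ratio with a control selected from cohort members who remain at risk". The Statistical Analysis Plan section repeats it, with cases "matched in a 1:1 ratio with controls selected from cohort members who remain nonmyopic at the same follow-up time point", and names the model: "Conditional logistic regression models will be used to estimate odds ratios and 95% CIs, adjusting for potential confounders". Study Design confines cohort-level and cross-sectional analyses to describing refractive and biometric change. The mixed models in the Statistical Analysis Plan section concern biometry. No model of incident myopia on the whole cohort is stated.

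The same article says who is measured. Study Design: "All participants are followed annually using standardized ophthalmic examinations and questionnaires". Examinations: "All the abovementioned metrics were collected at each follow-up visit". Data Collection and Follow-Up describes "questionnaire-based assessments conducted at baseline and at each annual follow-up visit". No laboratory assay, record abstraction or other measurement limited to sampled children is described.

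Study Design justifies the sampling by efficiency, preserved temporal order, less selection bias and the handling of age-dependent, time-varying exposures, adding: "Risk-set matching within the cohort facilitates appropriate control for age and follow-up time".

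**The concern.** Nested case-control sampling pays when exposure is costly to obtain, because it is then obtained only for cases and a few controls. Here the exposure data exist for everyone before any control is drawn. Sampling one control per case therefore sets aside observed data with nothing gained in return, and two equally correct draws of controls would give two different answers.

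The advantages claimed in Study Design do not need sampling. A time-to-myopia model compares each case with all children still at risk at that visit, so it keeps the temporal order, conditions on follow-up time and accepts time-varying exposures. Using everyone at risk also leaves no control selection to worry about.

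At stake is precision, chiefly for the moderate influencing factors that the Objective sets out to identify.

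**Working it through.** **The plan's own figures.** The article gives no power, precision or efficiency figure for the 1:1 analysis. Its sample size, 915 raised to 1006, reproduces as 915 × 1.10 = 1006.5. The 915 itself cannot be rebuilt, because no power, effect size or 3-year incidence is stated. Incidence and effect size below are therefore assumptions, shown over a range.

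**Weak effects (near the null).** Let d be the number of cases, h the annual incidence and Var(x) the exposure variance.

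- 1:1 conditional logistic: each pair contributes on average Var(x)/2, so information = d × Var(x)/2.
- All at-risk children, logistic with visit intercepts: each child-visit contributes h(1−h)Var(x). Since d = h × child-visits, information = d(1−h)Var(x).
- Share retained by 1:1 = 0.5/(1−h).

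| Assumed annual incidence | 3-year incidence, 1−(1−h)³ | Retained by 1:1 | Lost |
|---|---|---|---|
| 5% | 14% | 0.5/0.95 = 53% | 47% |
| 12% | 32% | 0.5/0.88 = 57% | 43% |
| 18% | 45% | 0.5/0.82 = 61% | 39% |

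**Stronger effects.** Simulation with 915 children, three annual visits and a standardised exposure, using model-based variances, gave these shares of full-cohort information retained by 1:1:

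| 3-year incidence | OR 1.5 per SD | OR 2 | OR 4 |
|---|---|---|---|
| 15% | 0.444 | 0.364 | 0.214 |
| 30% | 0.489 | 0.419 | 0.292 |
| 36% | 0.515 | 0.442 | 0.320 |
| 45% | 0.548 | 0.484 | 0.362 |

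An annual incidence of 12% lies between the 30% and 36% rows. Runs at or near that incidence put the loss at about 56 to 58% for OR 2 and 67 to 72% for OR 4. Both estimators stayed close to the true coefficient. The largest departure was for the 1:1 estimate at 15% incidence and OR 4: 1.446 against a true 1.386.

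**A moderate binary factor.** Assume 850 children at risk (for orientation, 915 × (1 − 0.059) = 861 if the cited prevalence at age 6 applied at baseline), 12% annual incidence, 50% exposed and OR 0.70.

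- Cases: 850 × (1 − 0.88³) = 271. Var(x) = 0.25.
- Near-null SE, 1:1: 1/√(271 × 0.25/2) = 0.172. Full risk sets: 1/√(271 × 0.88 × 0.25) = 0.130.
- Simulated SE at OR 0.70: 0.175 and 0.131. Variance ratio (0.175/0.131)² = 1.78.
- Normal-approximation power, with |ln 0.70| = 0.357: Φ(0.357/0.175 − 1.96) = 53% and Φ(0.357/0.131 − 1.96) = 78%. Simulation gives about 55% and 80%.
- Over annual incidence of 18% down to 5%, the simulated variance ratio runs from 1.66 to 1.94.

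**How much data is left out.** In this scenario there are 850 × (1 + 0.88 + 0.7744) = 2256 at-risk child-visits, and the matched analysis uses 2 × 271 = 542 of them (24%). Counted as children, about 56% enter at least once as case or control.

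**The case against.** The strongest reply is that this is a preference for efficiency and not an error. Risk-set sampling with conditional logistic regression is an established, valid method. The design is deliberate and consistent across sections, and the Sample Size Calculation section refers to it. That stands as far as validity goes. A reader might infer that the primary odds ratio will be biased; nothing in the documents supports that. The reply does not rescue the choice, because the article names no cost that sampling avoids.

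Second, the main exposure may be so strong that precision hardly matters. The Discussion cites a five-year school cohort in which incidence ran from 4.4% above +2.00 D to nearly 92% between 0.00 and −0.50 D. An effect of that size would be detected with matched pairs. This stands for detection, though the interval would still be wider than it need be. It does not cover the other influencing factors.

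Three stronger readings go too far:

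- That most children are discarded. This is true of child-visits but not of children at the incidence assumed above; it would hold for children only at low incidence.
- That at least half the information is always lost. For weak effects at high incidence the loss is nearer 40%.
- That age is left uncontrolled because the only stated matching variable is the follow-up time point. The Statistical Analysis Plan section lists age among the adjustment variables, and further matching details may sit in the full plan.

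**Conclusion.** The point holds as a loss of precision and reproducibility in the primary analysis, with no bias implied. That every child is measured at every visit, and that no saving is described, comes straight from the article. The size rests on assumptions, since the article gives neither incidence nor effect size. For annual incidence of about 5 to 18%, the loss is about 40 to 47% of full-cohort information for weak effects, and about half or more as the exposure strengthens. The practical consequence is a lower chance of identifying moderate factors, as in the OR 0.70 example. It should be changed, since the remedy costs little, but it does not undermine the study.

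**What to change.** Make the primary model of incident myopia use every at-risk child at each visit. Either discrete-time regression (logistic or complementary log-log) with visit-specific intercepts or a Cox model would serve. Adjust flexibly for age and take time-varying covariates from before the outcome visit. Keep the 1:1 conditional logistic analysis as a sensitivity analysis. The two should give similar answers but are not the same model: the likelihoods differ, and the wording should not call them equivalent.

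If sampling is retained as primary, use several controls per case. Near the null, four per case keep about 0.8/(1−h) of the information: 84%, 91% and 98% at annual incidence of 5%, 12% and 18%.

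The cost is rewording the primary analysis in Study Design and the Statistical Analysis Plan section, aligning the Sample Size Calculation rationale, and recording the change on the registry, as Ethical Considerations provides. The Results section says analysis begins only after data collection ends, so this can be done before any outcome analysis. No new data are required.
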